The number of children is based on an initial calculated requirement of 415 participants, with an additional 10% (rounded up from 456.5 to 460) added to account for potential dropouts or loss to follow-up. The sample is stratified based on administrative units and locality type and randomization is ensured by using the MS Excel function. Children will be included based on the enrolment in kindergarten, consent of the parents, and assent from the child. The exclusion criteria are represented by chronic general diseases or a history of allergic reactions, the presence of fluorosis or other enamel deficiencies, and non-collaborative behavior. The selection can be seen in the flowchart in Figure 1.

The nationally representative sample will be evaluated at baseline using self-assessment tools and clinical examination. During the intervention, evaluations will be performed every 6 months.

The program is designed to deliver additional clinical prevention activities through dental hygienists, aimed at children aged four to six, a special priority being afforded to nursery establishments, in order to improve the oral health of young children and complement the established national toothpaste/toothbrush scheme. The activity flow chart can be seen in the figure below (Figure 2).

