### 3.5. Statistical Methods for Primary and Secondary Outcomes

Caries activity levels after implementing the daily tooth-brushing scheme will be evaluated as the primary outcome. The outcomes will offer information regarding the particularities of the clinical investigation for the specific age group and the time necessary for the investigation and intervention. Clinical outcomes will be evaluated by using the caries incidence rate, calculated on each tooth as the unit of analysis and evaluated using a multi-step approach:

The net caries increment for initial, moderate, and extensive caries severity using ICDAS (Δ-initial, Δ-moderate, and Δ-extensive) will be calculated at each follow-up examination.

Events will be defined as a tooth receiving a lesion or as the sum of the Δ-caries changes in status recorded at the baseline examination, at the interim, and at the last examination. The number of events will be appraised by subtracting the number of caries-free teeth at the last examination from those at baseline.

Data analysis will be performed using SPSS version 24 (IBM Corp., Armonk, NY, USA) and the R software (R Core Team 2023). SPSS will be used for initial data cleaning, descriptive summaries, and basic inferential tests. R will be used for advanced modeling, intention-to-treat (ITT) analyses, and reproducible visualizations.

Data will be cleaned and validated prior to analysis. Descriptive statistics will be computed using continuous variables—mean ± SD (if normal), or median [IQR] (if non-normal) and categorical variables—counts and percentages. Baseline comparability between groups will be assessed but not tested for statistical significance (in accordance with CONSORT guidelines) [19]. Primary outcomes will be analyzed using the intention-to-treat (ITT) principle. The choice of statistical test depends on the outcome type. For continuous outcomes, linear regression adjusting for baseline, if available, will be used. Logistic regressions will be performed for binary outcomes and Poisson or negative binomial regression could be used for count data. For the longitudinal data, linear mixed models or generalized estimating equations (GEE) will be used to account for within-subject correlation. To explore relationships between secondary variables, correlation analysis will be performed.

The non-parametric Mann–Whitney U test will be applied to assess the differences across the mean number of events between groups.

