The efficacy of the treatment will be assessed following the indication of the CONSORT consensus guidelines including both PP (Per Protocol) and ITT (Intention to Treat) protocols to calculate the reduction in risk ratio (RR) and the related number needed to treat (NNT) value. An event will be defined as the change in status at tooth level, i.e., the development of a new lesion or the progression of an existing lesion to a more severe stage. Cox Proportional Hazards models will be run to assess the factors associated with caries change in status. Estimates will be reported in the hazard ratio (HR) and their respective 95% confidence interval (95%CI). For all the statistical analyses, the statistical significance will be set at α < 0.05.

The extent and pattern of missing data will be explored. If data are missing at random, multiple imputations will be used. Sensitivity analyses will compare complete cases with imputed datasets. A two-sided alpha level of 0.05 will be considered statistically significant. For multiple secondary outcomes, false discovery rate (FDR) or Bonferroni correction may be applied. The results will be presented with appropriate tables and figures, for reproducibility.

A major aim of the monitoring and evaluation is to collect data to inform and support the planned longer-term roll-out of the program. Process evaluation will, therefore, be a major component of the evaluation plan, as well as using statistical methods for analyzing primary and secondary outcomes and the reference to where other details of the statistical analysis plan can be found, if not in the protocol.

An assessment of the costs of managing dental caries will be obtained through the triangulation of information collected from the National Insurance House and cost data sourced online. Given the variation in the provision of subsidized care across Romanian regions and the scarcity of information on public sector health care costs, private treatment costs are used as a proxy to estimate the direct costs of dental caries.

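### The event count is compared by an unadjusted Mann-Whitney test described as a test of means, and no single analysis of the caries outcome is named as primary

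*Protocol article*

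**What the plan says.** All statements are in the protocol article.

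- **Between-group test (section 3.5).** "The non-parametric Mann–Whitney U test will be applied to assess the differences across the mean number of events between groups". No covariate, stratum or cluster term is attached to it.
- **Event count (section 3.5).** "The number of events will be appraised by subtracting the number of caries-free teeth at the last examination from those at baseline". Later the section gives a different definition, which also counts worsening of a lesion already present: "An event will be defined as the change in status at tooth level, i.e., the development of a new lesion or the progression of an" (the sentence goes on).
- **Adjustment (section 3.5).** "For continuous outcomes, linear regression adjusting for baseline, if available, will be used". For counts, "Poisson or negative binomial regression could be used for count data".
- **Other analyses (section 3.5).** Linear mixed models or GEE are planned for within-subject correlation. Both PP and ITT sets are used "to calculate the reduction in risk ratio (RR) and the related number needed to treat (NNT) value". Cox models are planned for factors associated with change in caries status. Significance is set at 0.05 for all analyses. FDR or Bonferroni correction is mentioned as a possibility for multiple secondary outcomes only.
- **Baseline data (section 2).** "The nationally representative sample will be evaluated at baseline using self-assessment tools and clinical examination".
- **Sample size (sections 2 and 3.2).** 415 children before dropout and 460 after, from two-sided alpha 0.05, power 0.9, SD 2, design effect 2 and dropout 10%. No numeric difference is given.

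**The concern.** The sentence that fixes the between-group test has three weaknesses.

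1. **It describes the test wrongly.** A rank test does not address a difference in mean events. It can reject when the means are equal and miss a difference in means when the distributions differ in shape. It also gives no estimate in teeth.
2. **It uses less than the trial collects.** Baseline caries can be expected to predict later caries, and the event count cannot be formed without the baseline examination. Yet the test has no place for baseline as a covariate.
3. **It does not match the design.** The sample size doubles the number of children for clustering. The Mann-Whitney test treats children as independent, and the mixed models or GEE are described only for repeated measurements on the same child.

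In addition, several analyses of the same outcome stand side by side and none is designated as the one that answers the null hypothesis. After the data are in, a reader could not tell which result was meant to decide the trial.

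**Working it through.** **Step 1. Reproduce the stated sample size.** Inputs from section 3.2: z = 1.96 and 1.28, SD 2, design effect 2. The difference d is not stated. The formula for two means is n per arm = 2 × SD² × (1.96 + 1.28)² / d².

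- Back-solving from 415 in total (415 / 4 = 103.75 effective children per arm): d = 2 × 3.24 × √(2 / 103.75) = 0.90.
- Forward check with d = 0.9: 2 × 4 × 10.4976 / 0.81 = 103.68 per arm; × 2 arms × design effect 2 = 414.72, i.e. 415.
- Dropout: 415 × 1.1 = 456.5, rounded up to 460 as stated.

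So 415 agrees with a comparison of two means with d = 0.9, but 0.9 is an inference. Reading 415 as per arm would imply 0.64, and a one-sided test would imply 0.81.

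**Step 2. Gain from baseline adjustment (illustrative).** Assume that SD 2 applies to the unadjusted outcome, that baseline correlates r with it (no value is given; range 0.3–0.6), and that the design effect stays at 2. The residual SD is 2√(1 − r²), and power = Φ(0.9 / [2√(1 − r²) × √(2 / 103.75)] − 1.96).

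| r | Residual variance removed (r²) | Power at 415 children |
|---|---|---|
| 0 | 0% | 90% |
| 0.3 | 9% | 92% |
| 0.5 | 25% | 96% |
| 0.6 | 36% | 98% |

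The gain depends little on the 0.9 itself. If 415 gives 90% power two-sided for whatever difference was used, the expression reduces to Φ(3.24 / √(1 − r²) − 1.96). With r = 0.5 that is Φ(3.74 − 1.96) = Φ(1.78) = 96%, the same result.

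**Step 3. Does Mann-Whitney test means?** Two groups of 207 children were simulated with equal means of 2 events but different spread (negative binomial with k = 1 against Poisson; assumed shapes; 4,000 trials). Mann-Whitney rejected in 72% of trials and a Welch test of means in 5.7%. The shapes were chosen to show the principle and are not a forecast for this trial.

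**Step 4. Rank test against adjusted regression.** In a simulated non-negative count with an assumed 30% reduction, 207 children per arm and no clustering (2,000 trials), power was 70% for the unadjusted Mann-Whitney test. It was 86% both for baseline-adjusted linear regression and for baseline-adjusted Poisson regression with robust standard errors.

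**Step 5. Clustering.** Section 3.3 does not make clear whether kindergartens or children are allocated to arms. If kindergartens are allocated and the design effect is really 2, a test that ignores it has a type I error of 2 × [1 − Φ(1.96 / √2)] = 2 × [1 − Φ(1.386)] = 16.6%. This figure does not apply if children are allocated individually within kindergartens.

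**Step 6. The two event definitions.** A loss of caries-free teeth cannot count progression in a tooth that was already carious, whereas the later definition does. The subtraction is net and can be negative if lesions reverse, which section 4 expects for incipient caries. The later definition cannot be negative. The model therefore depends on which definition is kept.

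**The case against.** **Baseline is not thrown away.** A reader might infer that the plan discards the baseline ICDAS. It does not: the event count is itself a change from baseline, and baseline-adjusted linear regression is planned for continuous outcomes. What stands is narrower: the named between-group test has no baseline covariate, and a change score is not a substitute for one.

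**No error rate across tests follows from the text.** A reader might also infer several competing primary tests with an inflated chance of a false claim, and put a number on it. The protocol nowhere says that one positive result among them suffices. Count regression is optional, the RR and NNT are effect measures with no test attached, and Cox is described as an analysis of associated factors. The supported criticism is that no primary analysis is designated.

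**Effect estimates are planned.** RR, NNT and HR will be reported, the HR with a 95% CI. Only an estimate on the scale of the tested event count is missing.

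**The power figures are conditional.** The difference and the correlation are not in the document, and section 3.2 also speaks of an odds ratio, so sizing on means is an inference from the SD. The calculation is a normal-theory one and not the power of Mann-Whitney itself. This is fair, and the figures are offered only as illustration.

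**Stratification.** The strata in sections 2 and 3.3 describe sampling and selection of nurseries, not allocation to arms. Adjusting for locality type is sensible for precision, but the text does not make it a requirement of the design.

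**Detail may sit in an analysis plan.** Covariate lists often do. But this article does not merely leave the test open: it fixes a specific test, describes it wrongly, and sets 0.05 for every analysis.

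**Conclusion.** The point holds in a limited form. The one test named for the event count is misdescribed as comparing means, takes no baseline covariate although baseline examination of the whole sample is planned, and ignores the clustering that the sample size allows for. No analysis of the caries outcome is named as primary.

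The illustrative gain from adjustment is from 90% to about 92–98% power. It rests on an assumed baseline correlation of 0.3–0.6, SD 2 for the unadjusted outcome, an unchanged design effect of 2 and the back-solved difference of 0.9. The type I error of 16.6% applies only if kindergartens are the unit of allocation and the design effect is truly 2.

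The availability condition on baseline ("linear regression adjusting for baseline, if available, will be used") is a minor point. It is written for continuous outcomes in general, but it makes no sense for a caries outcome computed from baseline.

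**What to change.** 1. **Reconcile the two event definitions in section 3.5 first**, and state which one is primary.
2. **Name one ITT primary analysis to match.**
   - For the net change in caries-free teeth: a linear mixed model (or GEE) of the child's value at the last examination, adjusted for the baseline number of caries-free teeth, age and locality type, with a kindergarten term. Report the adjusted mean difference with 95% CI.
   - For new or progressed lesions, which are never negative: negative binomial regression with the same covariates, a kindergarten term and an offset for teeth at risk. Report the adjusted rate ratio with 95% CI.
3. **Remove the availability condition for the caries outcome.** Reconcile section 2 with Table 1, which marks clinical outcomes only from T1 in the post-allocation columns, so that it is clear when the baseline covariate is measured.
4. **Label Mann-Whitney, Cox, RR/NNT and the PP analyses as supportive**, and describe Mann-Whitney as a comparison of distributions.

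**Cost:** no new data, since the baseline examination, age and locality are already planned. The work is a decision on the event definition and a rewrite of part of section 3.5, to be settled before outcome data are compared by group.

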## 1. Introduction

The 74th World Health Assembly recognized oral diseases as strictly correlated to other non-communicable diseases. Oral diseases represent a constant burden for both health care and socio-economic systems [1]. Dental caries and periodontal disease are the major oral diseases worldwide. In children under the age of 6, the disease, called Early Childhood Caries (ECC), occurs in children under the age of 6 and has a specific pattern that leads to significant modifications in the child’s functional development [2]. The disease is, nowadays, considered reversible if it is diagnosed in the early, non-cavitated stage, and can be halted even if indicators suggest microcavitation of the enamel. However, it remains the most common chronic disease in young children, and it has also been associated with poor quality of life for both affected children and their parents, affecting their ability to learn, causing missed school days, and incurring high costs for treatments [3]. The presence of ECC in very early childhood is linked to a higher risk of developing new caries lesions in the permanent dentition and an increased number of emergency dental visits due to caries complications [4].

Good behaviors and skills gained during early childhood are crucial for maintaining good oral health throughout life [4,5]. In addition to oral hygiene, there are several other factors that influence oral health status, such as attending dental visits, socio-economic status, or parental dental attendance, especially maternal attendance [4,5,6]. During adult life, healthy hygiene behaviors such as tooth brushing and additional dental hygiene measures are correlated to dental visits, dental plaque accumulation, the presence of calculus, and dental anxiety [7].

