## 2. Experimental Design

The study is designed and planned as an RCT, taking into consideration the early diagnosis of caries lesions through clinical examinations in the nurseries, control of risk factors through the evaluation of oral health-related knowledge, and behaviors, health education, and evaluation of the efficacy to arrest caries’ progression through the application of fluoride toothpaste. The trial will also develop new primary care teams—dental hygienists. This will provide a framework for integrating the prevention and control of dental caries into general health interventions.

In accordance with the informed consent, all personal data of the participants will be kept anonymous. The participants will receive a unique ID which will be used for data entry on an online software. The ID will be used for each clinical examination and data will be entered accordingly. As stated by Romanian regulations, an archive of the data has to be kept for 5 years after the trial in the secured archive of the university. The program was approved and registered by the Ethical Committee of the “Victor Babes” University of Medicine and Pharmacy Timișoara, Romania, under trial No. 18688/23.10.2023 and Protocol NCT06441500/28.05.2024 released on https://clinicaltrials.gov/, accesed on 29 May 2024, protocol version 1.

The project will be implemented in collaboration with the universities of Medicine and Pharmacy in Bucharest, Timișoara, Cluj-Napoca, Craiova, Iasi, and Targu Mures in order to ensure a homogeneous distribution of the evaluation sites, covering the whole country. The study group will consist of kindergarten children. The pathfinder sampling technique will be used to obtain a representative sample. Selection of nurseries will be performed according to the pathfinder sampling technique. As suggested by the World Health Organization (WHO), this survey’s design is suitable for the collection of data for planning purposes and monitoring of oral health programs in all countries regardless of the level of disease, availability of resources, or complexity of care.

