## 5. Discussion

Dentistry is undergoing a major paradigm shift from a surgical specialty to a medical specialty; therefore, non-operative treatment plans will become more and more central, and this project aims to add a step to the pyramid of evidence. The significance of this intervention represents an innovative approach of implementing daily tooth brushing, using fluoridated toothpaste, as part of a supervised, standardized, and routinely delivered public health strategy, as a protective measure to prevent new carious lesions, as well as for its therapeutic potential under real-life conditions.

Although the preventive and therapeutic effects of fluoridated toothpaste have been extensively studied, the specific research gap addressed by this study lies in the fact that it is used within a school-based oral health intervention targeting high-risk young children.

By integrating fluoride exposure through supervised tooth brushing into the daily routine of children in an institutional setting, this model offers a potentially more effective and equitable method of improving oral health, particularly in populations where access to regular dental care and parental supervision at home may be limited.

These characteristics are important taking into account the diverse socio-economic settings, with low access to professional dental care, where cost-effective, self-administered interventions like fluoridated toothpaste can play a crucial role in improving oral health status.

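### Section 3.5 scores the same tooth differently under its two sets of event rules, and neither gives a separate estimate of arrest or reversal of existing lesions

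*Protocol article*

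**What the plan says.** Section 3.5 gives more than one rule for what counts.

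- **Increments:** "The net caries increment for initial, moderate, and extensive caries severity using ICDAS (Δ-initial, Δ-moderate, and Δ-extensive) will be calculated at each follow-up examination".
- **Events, first rule:** "Events will be defined as a tooth receiving a lesion or as the sum of the Δ-caries changes in status recorded" at the baseline, interim and last examinations.
- **Counting rule:** "The number of events will be appraised by subtracting the number of caries-free teeth at the last examination from those at baseline".
- **Events, efficacy paragraph** (risk ratio and number needed to treat, followed by the Cox models): a change in tooth status, spelled out as "the development of a new lesion or the progression of an existing lesion to a more severe stage".

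The article claims two kinds of effect. Section 2 sets out to evaluate efficacy in arresting caries "progression through the application of fluoride toothpaste". Section 5 presents supervised brushing as preventing new lesions, "as well as for its therapeutic potential under real-life conditions". Section 1 says that the disease is now "considered reversible if it is diagnosed in the early, non-cavitated stage", and sections 4 and 5 cite reversal of incipient lesions as an effect of fluoride toothpaste.

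**The concern.** Prevention acts on sound teeth; arrest and reversal act on teeth that already have a lesion. The outcome rules do not keep these apart.

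The efficacy event counts only worsening. A healed lesion and an unchanged lesion both score zero, and a lower event rate could come entirely from fewer new lesions. The earlier rules do respond to healing, but only as a net count in which healing cancels new lesions, and they give progression no weight.

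Two things are at stake. The treatment effect depends on which rule the analyst applies, and a claim of arrest or therapeutic effect would have no estimate of its own behind it. Existing lesions are unlikely to be a marginal part of the data: section 5 reports that only 14% of 6-year-olds in the earlier national survey had dmft 0, so 86% had some caries experience.

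**Working it through.** **Inputs.** All rules come from section 3.5. States are sound (S), initial (I), moderate (M) and extensive (E).

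**Assumptions.** The article gives no formula for the net increment, so Δ is taken as teeth in the category at follow-up minus teeth in it at baseline. The same teeth are seen at both examinations.

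**Formulas, per tooth.**
- Sum = Δ-initial + Δ-moderate + Δ-extensive.
- Subtraction = caries-free at baseline minus caries-free at the last examination.
- Worsening event = 1 if the final state is more severe than the baseline state, otherwise 0.

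| Transition | Δ-initial | Δ-moderate | Δ-extensive | Sum | Subtraction | Worsening event |
|---|---|---|---|---|---|---|
| S to I | +1 | 0 | 0 | +1 | +1 | 1 |
| S to M | 0 | +1 | 0 | +1 | +1 | 1 |
| I to S (reversed) | -1 | 0 | 0 | -1 | -1 | 0 |
| I to I (unchanged) | 0 | 0 | 0 | 0 | 0 | 0 |
| I to M (progressed) | -1 | +1 | 0 | 0 | 0 | 1 |
| I to E (progressed) | -1 | 0 | +1 | 0 | 0 | 1 |
| M to E (progressed) | 0 | -1 | +1 | 0 | 0 | 1 |

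**Step 1: the rules conflict.** Progression of an existing lesion is 1 under the efficacy paragraph and 0 under the sum and the subtraction. Return to sound is 0 under the efficacy paragraph and -1 under the other two.

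**Step 2: Δ-initial alone is ambiguous.** It is -1 for I to S, I to M and I to E alike.

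**Step 3: the three Δ's together are also ambiguous once summed.** Two children each start with one sound tooth and one initial lesion.
- Child A: the lesion heals and the sound tooth becomes moderate. Δ's: (-1, 0, 0) + (0, +1, 0) = (-1, +1, 0). Sum 0, subtraction 1 - 1 = 0, worsening events 1.
- Child B: the sound tooth stays sound and the lesion becomes moderate. Δ's: (-1, +1, 0). Sum 0, subtraction 1 - 1 = 0, worsening events 1.

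Child A had a reversal and no progression; Child B had a progression and no reversal. Every planned count is the same for both.

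**Step 4: the same at group level.** The numbers are assumed, for illustration only. Each group has 20 new initial lesions. Δ-initial = 20 - healed - progressed; Δ-moderate = progressed; worsening events = 20 + progressed; subtraction = 20 - healed.

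| Healed | Progressed | Δ-initial | Δ-moderate | Sum | Subtraction | Worsening events |
|---|---|---|---|---|---|---|
| 30 | 10 | -20 | +10 | -10 | -10 | 30 |
| 10 | 30 | -20 | +30 | +10 | +10 | 50 |
| 0 | 10 | +10 | +10 | +20 | +20 | 30 |

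Rows 1 and 2 share Δ-initial although healing and progression are exchanged. Rows 1 and 3 share the worsening count although 30 lesions healed in one and none in the other.

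**The case against.** A reader might infer that reversal goes uncredited throughout the plan, and that the arrest aim is out of reach. The documents support neither.

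- **Reversal is credited in part.** The summed Δ's and the caries-free subtraction both score a return to sound as -1.
- **Arrest is partly visible.** Arrest is absence of progression, and progression is inside the worsening event, so successful arrest would lower that event count. Pooling with new lesions makes the result less specific; it does not remove it.
- **Δ-initial does not stand alone.** Δ-moderate and Δ-extensive are planned at the same visits and, for a single tooth, do separate healing from progression. This defence fails once the Δ's are summed over a child or group, as step 3 shows.
- **Reversal is not in the formal hypothesis.** Section 1.1 speaks only of caries status, the therapeutic claim is Discussion text, and a worsening-only incidence outcome is legitimate. That is a good reason to keep the worsening event. But arrest is named in section 2 as something the trial will evaluate, and the conflict between the event rules lies within section 3.5 whatever the objectives are.

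It can also be said that a split by baseline state is a detail for an analysis plan not shown here. That would hold if the article were silent. It instead states several rules that disagree.

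**Conclusion.** The point holds in this form: the efficacy event excludes reversal and pools new lesions with progression, while the earlier rules in section 3.5 are net and contradict it. The disagreement is one full event per progressed tooth (1 against 0) and one per tooth returned to sound (0 against -1). Arrest and therapeutic effect contribute to some of the counts, but neither has a separate interpretable estimate.

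The per-tooth scores for the sum and the Δ's rest on reading Δ as change in category counts. The subtraction rule and the worsening event do not need that reading, so the conflict between those two stands without it. The article gives no healing or progression rates for the two groups, so no expected effect on the trial result can be computed; the group table shows only how the rules behave.

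**What to change.** 1. Make the worsening event in the efficacy paragraph the single event definition. Drop the summed-Δ and caries-free subtraction rules, or reconcile them with it and relabel them as net descriptive measures.
2. Replace the stage-specific increments with cumulative thresholds: any lesion; moderate or worse; extensive. Initial-to-moderate progression then scores (0, +1, 0) and return to sound (-1, 0, 0), so worsening can no longer lower a count.
3. Report by baseline state and group: (a) teeth sound at baseline, any new lesion (prevention); (b) teeth with an initial or moderate lesion at baseline, classed as reversed, unchanged or progressed. Name (b) as the secondary estimate for arrest and therapeutic effect.

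Step 3 is needed as well as step 2, because Child A and Child B both still score (0, +1, 0) on the thresholds and only the split by baseline state separates them.

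**Cost.** Analysis wording only; tooth-level ICDAS assessments are already planned at the clinical examinations. It adds one secondary outcome under the multiplicity rule. The reversed class will carry some misclassification: section 3 has children examined without air-drying, while code 1 lesions are described there as visible only after drying. That should be stated when (b) is reported.
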